### Participant timeline

The time schedule of this study, including enrolment, interventions, assessments, and visits for participants, is shown in Fig. 1.

### Sample size

The sample size calculation was performed using the PASS15 software, version 15.0.5, with reference to a prior randomized controlled trial that reported the value of targeting CXCR4 with 68Ga-Pentixafor PET/CT for subtyping P.A., which enrolled 120 cases [19]. According to this study protocol, a sample size of 60 participants in each group was calculated to sufficiently detect the target effect size (0.5) with a type I error of 5% (*α* = 0.05) and 90% power (*β* = 0.10) by the PASS15.0 software. Allowing for a 20% loss to follow-up, this study was designed to include 120 cases.

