#### Primary outcome

Rate of biochemical remission

Biochemical outcome evaluation in 3 and 6 months after AVS: serum potassium, orthostatic ARR. All these data will be recorded in the PASO table [11] (feasible criteria for the classification of outcomes of adrenalectomy for the treatment of unilateral primary aldosteronism). The detailed criteria of complete, partial, and absent biochemical remission are shown in Fig. 3.

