### Assignment of interventions: allocation

#### Allocation-sequence generation

Random numbers within the range of 1 to 120 will be generated by an independent statistician using the SPSS V25.0 software. The allocation of participants will be determined based on the parity of the generated random numbers. Participants with an odd random number were assigned to the 15-min group, and participants with an even random number were assigned to the 2-h group.

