### Statistical analysis

An independent statistician will complete the statistical analysis of the study result via the SPSS V25.0. Baseline characteristics will be described by descriptive statistics. *x̅* ± *s* will represent continuous variables with the normal distribution, and the *t* test will compare the differences between the two groups. The Mann–Whitney *U* test will be used in continuous variables that were not normally distributed. Categorical variables will be expressed as frequency (%), and the chi-square test will be used to compare the differences between the two groups. Effect estimates will be provided with corresponding 95% confidence intervals, and *P* values ≤ 0.05 will be considered statistically significant. All randomized participants will be included in the analyses, and data will be analyzed in the group where the participants were randomized initially. The experimental group includes the available data from the 15-min supine group, and the control group includes the available data from the 2-h supine group. The principles of intention-to-treat analysis will be used to preserve the unique benefit of randomization, regardless of whether that participant received the allocated intervention. Multiple imputation (MI) using the mice package in R will be applied to analyze the missing data.

Further secondary analyses will include pre-specified subgroup analyses according to age and the two stratification/minimization variables, investigated by introducing the relevant interaction with treatment allocation into the regression model. In addition, to assess the stability of any intervention effect, we will fit a mixed model for the primary outcome at 3 and 6 months, adjusted for baseline measures.

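### The sample-size paragraph gives 60 per group both before and after a 20% loss allowance, and its stated inputs do not lead to 60

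*Protocol article*

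**What the plan says.** All the figures stand in one paragraph of the protocol article, under Sample size. The requirement is put as "a sample size of 60 participants in each group was calculated to sufficiently detect the target effect size (0.5"). The calculation is said to come from PASS 15, at α = 0.05 and power 0.90. The next sentence reads "Allowing for a 20% loss to follow-up, this study was designed to include 120 cases". The paragraph also refers to an earlier imaging study in primary aldosteronism that enrolled 120 cases.

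The paragraph does not say what kind of effect size 0.5 is, whether the test is one- or two-sided, or what remission rates or standard deviation were assumed.

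Elsewhere in the article, the primary outcome is "Rate of biochemical remission", graded complete, partial or absent. The Statistical analysis section assigns the chi-square test to categorical variables, and P "values ≤ 0.05 will be considered statistically significant". Allocation is by odd or even number from 1 to 120, so 60 per arm is the intended split.

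**The concern.** Two things do not fit. First, the same 60 per group serves as the calculated requirement and as the number after allowing for loss; with a 20% allowance these must differ. Second, an effect size of 0.5 at 5% and 90% power is a familiar combination, and its usual answer is not 60 per group.

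This matters for how the result will be read. Under Trial design, the working hypothesis is that a shorter supine time makes no difference to subtyping, and no margin is given. A non-significant result is therefore what the investigators expect, and readers would lean on the 90% figure to judge how much difference it excludes. That figure has to be traceable to the primary outcome and to the number of patients who will actually be analysed.

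**Working it through.** **Inputs from the Sample size section:** effect size 0.5, α = 0.05, power 0.90, 60 per group, 20% loss, 120 in total. **Assumed because not stated:** the metric and the sidedness. Two-sided is the natural reading of the planned tests; one-sided is shown as well.

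**1. The loss allowance (no assumption about metric or sidedness needed)**

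- If 60 per group must be evaluable: 60 / (1 − 0.20) = 75 per group, 150 in total.
- If 120 already includes the loss: 60 × (1 − 0.20) = 48 evaluable per group, 96 in total.
- The paragraph gives 60 in both roles.

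**2. Trying to reproduce 60 (or 48, which becomes 60 after loss)**

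For a standardised difference, n per group = 2 × [(z for α + z for power) / 0.5]².

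- Two-sided: 2 × [(1.960 + 1.282) / 0.5]² = 84.06, so 85 per group for Cohen's h, or for d by the normal formula. The exact t calculation for d gives 86.
- One-sided: 2 × [(1.645 + 1.282) / 0.5]² = 68.5, so 69; exact t for d gives 70.

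For the chi-square effect size w, total N = λ / w², where λ is the noncentrality that gives 90% power.

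- 1 df: 10.51 / 0.25 = 42.03, so 43 patients in total.
- 2 df: 12.65 / 0.25 = 50.6, so 51 in total.

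Other readings of 0.5, two-sided unless noted:

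| Reading | Per group |
|---|---|
| Risk difference 0.5, over a range of rates | 16 to 23 |
| Odds ratio 0.5, reference rates 50% to 95% | 177 or more |
| Non-inferiority margin of 0.5 SD, one-sided 2.5% or 5% | 85 or 69 |
| Equivalence margin of 0.5 SD | 87 or more |

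None of these gives 60 per group, or 48 before loss. A match appears only with an input that the text lacks or contradicts:

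- A risk ratio of 0.5 with assumed rates of 65% v 32.5% gives 47.6, so 48 per group, and 48 / 0.8 = 60. With a reference rate of 60% the figures are 56 and 70; with 70% they are 41 and 52.
- One-sided testing at 80% power gives 50 per group, and 50 × 1.2 = 60, but the stated power is 90%.

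**3. Power of the stated design at 0.5**

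| Reading of 0.5 | 60 per group | 48 per group |
|---|---|---|
| d, two-sided (exact t) | 77.5% | 67.9% |
| d, one-sided (exact t) | 85.9% | 78.4% |
| w, 1 df | over 99.9% | 99.8% |
| w, 2 df | 99.9% | 99.5% |

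On the two-sided d reading, 90% power is reached at d = 0.60 with 60 per group and d = 0.67 with 48. For a balanced 2×2 table, w = 0.5 corresponds to, for example, 75% v 25%: w = 0.50 / (2 × √(0.5 × 0.5)) = 0.5, a 50-point difference.

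**4. Precision on the remission scale with 48 per group**

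Half-width of the 95% CI for a difference, equal rates p in both arms: 1.96 × √[2p(1 − p) / 48].

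- p = 0.80: 1.96 × √(0.32 / 48) = 0.160.
- p = 0.50: 1.96 × √(0.50 / 48) = 0.200.

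These rates are illustrative; the article gives none.

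**The case against.** The best defence is that the article never says 0.5 is a standardised difference between means. The primary outcome is categorical and the planned test is chi-square, whose own effect-size index is w. On that reading 120 patients give far more than 90% power. Sidedness is not stated either, so any single power figure depends on a choice made by the reader. And a risk ratio of 0.5 with a 65% reference rate gives 48 per group and exactly 60 after loss.

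Most of this stands. A reader might infer that the trial simply has 68 to 78% power, or that no calculation could lead to 60. The article supports neither: the first needs a two-sided test and d or h as the metric, and the second is refuted by the risk-ratio example. That example does not rescue the paragraph, however. Its 65% appears nowhere, the answer moves quickly with the reference rate, and it makes 48 the requirement, whereas the text says that 60 is.

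The w reading does not help either. It does not give 60 per group, and it would mean planning for about a 50-point difference in remission in a trial that expects none.

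It could also be said that an article condenses a fuller protocol. That would excuse missing rates, but not two stated figures that cannot both hold.

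Finally, the imaging study is cited alongside a software calculation, so it should not be called the sole basis for 120. It addressed a different question, and its enrolment does not justify this trial's total.

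**Conclusion.** The point holds. The contradiction over loss is certain and rests on no assumption: the total is either 150 with 60 evaluable per group, or 120 with 48. It is also established that 60 per group cannot be reproduced from the inputs as stated, because the metric, sidedness and remission rates needed to do so are missing.

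The effect on power is conditional. If 0.5 is a standardised difference, power is 68 to 78% two-sided or 78 to 86% one-sided, for 48 to 60 evaluable per group; all of these are below 90%. If 0.5 is w, power exceeds 99%, but for a difference of a size that would not bear on the trial's question. On any of the readings examined, the 90% claim cannot be tied to the remission rate with the information given.

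**What to change.** Revise the Sample size paragraph, without enrolling more patients:

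- State that 120 will be randomised and that, after 20% loss, 48 per group are expected to be evaluable; drop the statement that 60 per group is the calculated requirement. If the sponsor's calculation did require 60 evaluable, say so and acknowledge that 120 does not provide for the loss.
- Name the effect-size metric, the sidedness and the assumed remission rates.
- Replace the 90% claim with the power or precision that 48 per group gives for the remission rate under those rates. For example: with 48 evaluable per group, the 95% confidence interval for the difference in remission has a half-width of about 16 percentage points if both rates are 80%, and about 20 if both are 50%. These rates are placeholders for the sponsor's own.
- Do not use the imaging study's 120 cases as support for the total.

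The cost is a few sentences, and probably a less favourable statement of what the trial can show.

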### Recruitment

Some efforts will be made to ensure enough participant enrollment in this study: more than 200 patients were eventually diagnosed as P.A. in our centers, and 100–120 AVS surgeries were performed each year in our centers with a success rate higher than 95%. Therefore, we think we need 1–1.5 years to enroll enough cases. Besides, we would implement a poster recruitment strategy in our hospital and on the Internet, which contains detailed information about this trial’s objective, contact method, and attention matters. Further, a specific member will help interested participants to complete registration for the trial.

### Assignment of interventions: allocation

#### Allocation-sequence generation

Random numbers within the range of 1 to 120 will be generated by an independent statistician using the SPSS V25.0 software. The allocation of participants will be determined based on the parity of the generated random numbers. Participants with an odd random number were assigned to the 15-min group, and participants with an even random number were assigned to the 2-h group.

#### Allocation—concealment mechanism

The result of random sequences will be placed into specific envelopes. These envelopes will be prepared by individuals who are not directly involved in the trial. After enrolled participants signed the informed consent, they will be given a sealed envelope to open.

### Assignment of interventions: blinding

This trial is open-label with blinded outcome assessors so unblinding will not occur. A third party will oversee the management to ensure the confidentiality of the study until the completion of the data analysis.

### Data collection and management

#### Plans for assessment and collection of outcomes

Basic information will be collected during the initial assessment and enrollment. Participants will complete and sign a questionnaire including basic characteristics (such as gender, age, education, marital status, height, and weight) and medical history. The data collection will be accomplished by a staff not involved in the study. Data will be collected at five time points: during screening, baseline, after AVS, at 3-month follow-up, and at 6-month follow-up. To ensure the data quality, all collected information will be securely stored in an electronic database, the access to which will be only restricted to specific statisticians. After 3 years, all data will be deleted.

#### Plans to promote participant retention and complete follow-up

To ensure the completion of the follow-up, all participants will be informed of the benefits and offered compensation for completing assessments. Regular phone reminders will be conducted during the follow-up period.

#### Confidentiality

All information and data can only be accessed by authorized accounts and authorization can only be granted by the chief investigator. Participants’ information will be encoded with a specific ID number to keep confidentiality. The database will be protected on a secured platform.

#### Additional consent provisions for collection and use of participant data and biological specimens

No biological specimens will be collected in this study.

### Statistical analysis

An independent statistician will complete the statistical analysis of the study result via the SPSS V25.0. Baseline characteristics will be described by descriptive statistics. *x̅* ± *s* will represent continuous variables with the normal distribution, and the *t* test will compare the differences between the two groups. The Mann–Whitney *U* test will be used in continuous variables that were not normally distributed. Categorical variables will be expressed as frequency (%), and the chi-square test will be used to compare the differences between the two groups. Effect estimates will be provided with corresponding 95% confidence intervals, and *P* values ≤ 0.05 will be considered statistically significant. All randomized participants will be included in the analyses, and data will be analyzed in the group where the participants were randomized initially. The experimental group includes the available data from the 15-min supine group, and the control group includes the available data from the 2-h supine group. The principles of intention-to-treat analysis will be used to preserve the unique benefit of randomization, regardless of whether that participant received the allocated intervention. Multiple imputation (MI) using the mice package in R will be applied to analyze the missing data.

Further secondary analyses will include pre-specified subgroup analyses according to age and the two stratification/minimization variables, investigated by introducing the relevant interaction with treatment allocation into the regression model. In addition, to assess the stability of any intervention effect, we will fit a mixed model for the primary outcome at 3 and 6 months, adjusted for baseline measures.

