**Methods/design:**

This is a multi-center prospective randomized controlled study. One hundred twenty patients diagnosed as P.A. and willing for AVS examination will be included. Participants will be randomly allocated to a 15-min supine time group or 2-h supine time group. The primary outcome is the degree of biochemical remission (serum potassium and orthostatic ARR). The secondary outcomes are degrees of clinical remission (blood pressure, type and dose of antihypertensive drugs), the technical success rate, and the adverse event of AVS (selective index ≥ 2 is considered successful surgery without corticotropin stimulation).

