### Outcomes

#### Basic information

Before treatment, researchers will collect basic characteristics (such as gender, age, education, marital status, height, and weight) and medical history (such as blood pressure, type and dose of antihypertensive drugs, serum potassium, orthostatic ARR) of recruited participants.

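### By default the primary comparison is an unadjusted chi-square test that ignores the grading of biochemical remission and the baseline potassium and ARR already collected

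*Protocol article*

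**What the plan says.** All references are to the protocol article.

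- **Form of the outcome.** The abstract says "The primary outcome is the degree of biochemical remission (serum potassium and orthostatic ARR". The Primary outcome section is labelled "Rate of biochemical remission" but then points to three levels: "The detailed criteria of complete, partial, and absent biochemical remission are shown in Fig. 3". Assessment is at two visits: "Biochemical outcome evaluation in 3 and 6 months after AVS: serum potassium, orthostatic ARR".
- **Test.** Statistical analysis gives one rule for categorical variables: "the chi-square test will be used to compare the differences between the two groups". No other test is named for the primary comparison.
- **Baseline data.** Basic information lists "medical history (such as blood pressure, type and dose of antihypertensive drugs, serum potassium, orthostatic ARR) of recruited participants" as collected before treatment. Two of these, potassium and ARR, are the components of biochemical remission.
- **Adjustment.** It appears once, in an added analysis of the stability of any effect: "we will fit a mixed model for the primary outcome at 3 and 6 months, adjusted for baseline measures". The subgroup paragraph also refers to a regression model for interaction terms, but that model is not described and is not the treatment comparison.

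**The concern.** If the three grades are compared by a chi-square test, the 2×3 table has 2 degrees of freedom. The test then spreads its power over patterns that nobody expects, such as more partial responders at the expense of both ends, and it yields no single effect estimate, although the same section promises estimates with confidence intervals. On either form of the outcome, the test also leaves unused the two baseline measurements most likely to predict remission.

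This matters in a trial of 120 patients with a 20% loss allowance. The Trial design section hypothesises that shorter supine time leaves efficacy unchanged. An insensitive test makes a non-significant result more likely, and such a result could be misread as support for that hypothesis.

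**Working it through.** **Inputs from the article.** 60 per arm, 20% loss, effect size 0.5 on an unstated scale, α = 0.05, power 90% (Sample size). If the full loss occurs, 60 × 0.8 = 48 per arm are evaluable. Multiple imputation is planned, so the information available lies between these two numbers.

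**The plan's own figure.** If 0.5 is a standardised mean difference, two-sided, then n = 2(1.960 + 1.282)²/0.5² ≈ 84.1, so 85 per arm. Power is Φ(0.5·√(n/2) − 1.96): 78% at n = 60 and 69% at n = 48. The stated 90% is not reproduced on that reading. This is a separate issue; it is used here only to show that there is no spare power.

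**Assumed, because the article gives no remission rates.** Control split 70/20/10 (complete/partial/absent) and a common odds ratio of 2.5 against the shorter time.

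- Complete: odds 0.70/0.30 = 2.333; divided by 2.5 gives 0.933, probability 0.483.
- Complete or partial: odds 0.90/0.10 = 9; divided by 2.5 gives 3.6, probability 0.783.
- Comparison arm: 0.483 / 0.300 / 0.217.

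**Chi-square on three grades, 2 df.** Noncentrality λ = n·Σ(pᵢ − qᵢ)²/(pᵢ + qᵢ) = n(0.0399 + 0.0199 + 0.0434) = 0.1033n.

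- n = 48: λ = 4.96, power 50% (simulated 51%).
- n = 60: λ = 6.20, power 60% (simulated 60–61%).

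**Complete versus not, 1 df.** Power = Φ[(0.217 − 1.96·s₀)/s₁], with s₀ the pooled and s₁ the unpooled standard error.

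- n = 48: s₀ = 0.1003, s₁ = 0.0979, power 58% (simulated 59%).
- n = 60: s₀ = 0.0897, s₁ = 0.0875, power 68% (simulated 69%).

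**Ordered test.** This is the tie-corrected Wilcoxon test, equivalent to the proportional-odds score test, by simulation with 20,000 runs per scenario.

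| Per arm | Chi-square, 3 grades | Complete vs not | Ordered |
|---|---|---|---|
| 48 | 51% | 59% | 61–62% |
| 60 | 60–61% | 69% | 70–71% |

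The ordered test gains about 10 points over the three-grade chi-square and about 2–3 points over the binary comparison.

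**Sensitivity to the assumptions.** With control splits from 90/6/4 to an even three-way split, and odds ratios equivalent to 2 to 3, the gain over the three-grade chi-square is about 6–12 points. The gain over the binary comparison is −1 to +3 points when 70–90% of controls are complete, and up to about 21 points with an even split.

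**Baseline adjustment.** Logistic model for complete remission with one standardised covariate, 1,500 simulated trials, unadjusted → adjusted power:

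| Log-odds slope per SD | 48 per arm | 60 per arm |
|---|---|---|
| 0.5 | 71% → 73% | 81% → 82% |
| 1.0 | 59% → 65% | 71% → 77% |
| 1.5 | 49% → 61% | 58% → 70% |

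The gain is about 1–12 points. These power levels correspond to an odds ratio near 3. At 2.5 the unadjusted power at 48 per arm is roughly 12–20 points lower (about 51%, 42% and 37%), so this table must not be added to the previous one.

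A linear approximation points the same way. Dividing the SD by its adjusted fraction, power is Φ(0.5·√(n/2)/√(1 − R²) − 1.96). With assumed R² of 0.1, 0.2 and 0.3, 78% becomes 82%, 86% and 91% at 60 per arm, and 69% becomes 73%, 78% and 83% at 48 per arm.

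**The case against.** The best defence has five parts.

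1. **The chi-square sentence is generic.** It follows the description of baseline characteristics and is never designated as the primary test. The label of the primary outcome as a rate may mean complete versus not. This stands: the 10-point figure holds only for the three-grade reading. The lack of adjustment holds on both readings.
2. **An unadjusted chi-square is valid under randomisation.** This stands: the issue is efficiency and the lack of a clear effect estimate, not type I error.
3. **A reader might infer that the adjusted model is impossible because remission has no value at entry.** The documents do not support that. The adjustment is for baseline measures, and potassium and ARR are measured before treatment.
4. **A reader might infer that the mixed model is an ordinary linear one, unsuited to a categorical outcome.** The article never says linear. A mixed model with a categorical link fits its wording, and an article may leave the link and the covariate list to a fuller document.
5. **More power for a difference test does not answer a hypothesis of no effect.** This stands: the hypothesis has no margin, and better analysis does not replace one.

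**Conclusion.** The concern holds as a point of efficiency. As written, the primary comparison falls by default to an unadjusted chi-square test, while an ordered grading and two relevant baseline measures are left out of it.

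The cost of ignoring the order is about 10 points of power at 48–60 per arm if three grades are tested under the assumed 70/20/10 split and odds ratio 2.5, but only about 2–3 points if the outcome is complete versus not. The gain from one prognostic covariate is about 1–12 points for slopes of 0.5–1.5 per SD and an odds ratio of 2.5–3. None of these rates, odds ratios or slopes comes from the article; the ordering result also assumes proportional odds, and the covariate gain depends on how well potassium and ARR predict remission here.

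The change should be made because it is nearly free. The trial's validity does not depend on it.

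**What to change.** 1. State whether the primary outcome is the three-level grade or complete versus not, and at which visit.
2. Make the primary analysis the matching regression: proportional odds for the grades, logistic for the binary form. Adjust for centre, baseline serum potassium and log baseline ARR. Report the adjusted effect, including a standardised risk difference for complete remission, with 95% CI.
3. Use the same covariates and a categorical link in the 3- and 6-month mixed model. The primary regression can then also carry the subgroup interaction terms.
4. Keep the chi-square test as a supportive unadjusted result.

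**Cost.** Wording and routine programming before outcome data are seen; no extra patients, visits or measurements. The graded form relies on proportional odds. The model has five coefficients beyond the intercept(s): arm, two for the three centres, potassium and ARR. Under the assumed scenario about 48 × 0.30 + 48 × 0.517 ≈ 39 patients would lack complete remission, or about 8 per coefficient. If remission is much more common, a shorter covariate list should be fixed in advance. A choice between the graded and binary primary form should bear in mind that the binary form does not deliver the gain from ordering. The margin needed to support a conclusion of no effect has to be set separately.
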